#### JOINT SUPPORT training programme

The first session will aim to start within 6 weeks from consent. Sessions will be provided to both patient and caregiver participants by either a physiotherapist or occupational therapist. Irrespective of delivery method, each session will be up to 60 min. Throughout the five sessions, the JOINT SUPPORT healthcare professional will monitor the patient–caregiver competencies, providing continual feedback and critique to support the training. There will be a cognitive-behavioural approach used throughout the sessions, underpinned by social cognitive theory where dyads will be facilitated by a JOINT SUPPORT healthcare professional on the following topics:

##### Session 1

Understanding pain, caregiving and how pain affects the caregiving dyad.Introduction and explanation of the JOINT SUPPORT Workbook, highlighting material on pain and effects on the dyad.

##### Session 2

Pacing and graded activity.Goal setting.JOINT SUPPORT Workbook—highlighting material on goal-setting and problem-solving.

##### Session 3

Benefits of physical activity (reducing deconditioning, healthy ageing, physical and psychological health).Fear avoidance.JOINT SUPPORT Workbook—highlighting material on physical activity and fear avoidance.

##### Session 4

Medication use and management.JOINT SUPPORT Workbook—highlighting material on medication use and management.

##### Session 5

Working through case-study scenarios to re-enforce knowledge and critique competencies on JOINT SUPPORT skills.JOINT SUPPORT Workbook—highlighting material on case-scenarios and long-term goal setting.Confirmation of dates for JOINT SUPPORT telephone booster calls.

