#### JOINT SUPPORT telephone booster calls

Following the five group-sessions, a JOINT SUPPORT healthcare professional will telephone each caregiver and patient as a dyad during Week 1, 3 and 6 post-group session discharge. Each call is expected to take approximately 20 min. Both the caregiver and patient participant should be in the same room during these calls. Topics covered in each call will include:

Recovery progress and current status based on patient–caregiver shared goals.Discussion on JOINT SUPPORT Workbook use and progress including goal-setting sheets.Support to create collaborative goals and positive reinforcement for continued recovery.

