### Assessment

The data collection schedule is summarised in table 1.

**Table 1 T1:** Participant timeline illustrating schedule of enrolment, interventions and assessments

Time point	Screening and initial contact	Baseline	Randomisation	Group-based session	Post-session call	Follow-up
		Aim up to 14 days post-first contact		Weeks 1 to 5	Aim up to 6 weeks post-group-based session	3 months from post-randomisation (±3 weeks)
ENROLMENT						
Initial approach						
Informed consent						
Randomisation						
INTERVENTIONS						
Experimental (usual care plus JOINT SUPPORT)						
Control (usual care)						
ASSESSMENTS						
Screening logs						
Adverse event reporting						
Date of first appointment						
Patient age						
Patient gender						
Patient ethnicity						
Patient height						
Patient weight						
Patient medical history						
Patient occupational status						
Patient residential status						
Patient EQ-5D-5L						
Patient MSK-HQ						
Patient GSE						
Patient NRS pain						
Patient NRS fatigue						
Patient CES-D						
Patient Health Use Questionnaire						
Caregiver EQ-5D-5L						
Caregiver CES-D						
Caregiver Zarit Burden Questionnaire						
Caregiver Leisure Time Satisfaction Questionnaire						
Caregiver Health Use Questionnaire						
Caregiver age						
Caregiver gender						
Caregiver ethnicity						
Caregiver medical history						
Caregiver caregiving experience (duration/caregiver for another person)						
Caregiver residential status to patient						
Caregiver occupational status						
Working or not						
HCP usual care logs						
JOINT SUPPORT intervention logs						
Patient complications/adverse events						
Caregiver intervention home logs						
Caregiver acceptability intervention						
Patient–caregiver semi-structured interviews						
HCP semi-structured interviews						

CES-D, Centre for Epidemiologic Studies Depression Scale (CES-D); EQ-5D-5L, EQ-5D 5 level instrument; GSE, general self-efficacy scale; HCP, healthcare professional; MSK-HQ, Musculoskeletal Health Questionnaire; NRS, numerical rating scale.

To answer our feasibility objectives, we will assess:

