#### Data collection

Interviews will aim to be conducted up to 6 weeks post-intervention via telephone or video call, at a time convenient to dyads and healthcare professionals. This allows exploration and reflection of the patients’ and caregivers’ study experience once the intervention has ended in a reasonable recall period. Interviews will be semi-structured, following an open-ended question schedule, with a maximum duration of 60 min. Open-ended questions will explore the acceptability of the research based on Sekhon *et al*’s^37^ acceptability framework including the values of the intervention, burden, perceived effectiveness, self-efficacy and suggestions for improvement from their perspectives. Interviews will be conducted by a qualitative researcher (AW), closely supervised by a senior qualitative researcher (SH).

Prior to conducting the interview, consent will be obtained and audio-recorded from the participant. The interview will then follow a semi-structured, open-ended question schedule (table 3; table 4). Broadly, participants will be asked their attitudes towards topics including the:

Timing, frequency, duration and content of the JOINT SUPPORT training programme and telephone booster calls.Support and training provided for the group-based programme and telephone boosters.Recording of both components of the JOINT SUPPORT programme.Logistic of managing the participant flow.Their views on the recruitment process.Acceptability of the JOINT SUPPORT programme.Potential modifications or recommended changes to the JOINT SUPPORT programme.Perceived effectiveness/helpfulness.

**Table 3 T3:** Interview topic guide for the caregiving dyad interviews

The interview will be structured on the following areas of interest	Sample questions
Introduction	Overall, could you share your experiences of being involved with our research?
Determining participant views of their intervention	First of all, can you talk me through what study treatment you received? (prompt—clarify what was JOINT SUPPORT and what was usual care/non-study intervention)
The approach and consent process and willingness to be randomised to either group	Can you talk me through how you got into the study? You were allocated to X group. What did that feel like? Could we have dealt with that differently?

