The acceptability of the care (both groups)	Would you be happy to talk me through your treatment? As X’s carer, what was your impression of the care. For both of you, what was helpful and less helpful to your care?
Group-based JOINT SUPPORT programme and telephone booster calls (experimental group)	How far did you find the JOINT SUPPORT programme helpful—for both of you. Can you give specific examples? What didn’t work as well? Did you get the telephone calls from the trial team? Can you remember what you talked about? Can you give specific examples of what was helpful, and l helpful? Was there any advice that confused you or you weren't clear about?
What the strengths of the experimental intervention (perceived effectiveness)	What were the most helpful/good-bits of your JOINT SUPPORT intervention? What was good about it What didn’t you like about it?
What the weaknesses of the experimental intervention	What were the less helpful/worse bits of the JOINT SUPPORT intervention?
What modifications they may recommend to interventions received (standard care and experimental groups)	What could we improve? (prompt: What do you think is lacking?) How do you think we could better support you and your carer to support you with chronic pain?
The risk of intervention contamination between the groups	Did you talk to any other patients or caregivers while in hospital about the intervention? Was there any discussion between those who received it and did not receive it?
The ease and convenience of the data collection processes (baseline and 3 months) (all participants)	As you were part of a trial, we had to collect a lot of measurements. Can you talk me through what these were? How easy were they? How convenient were they? Overall, do you have any points to make about the testing?
Applicability of the methods and measures used	How did you manage with the questionnaires we gave you at the start of the study and at the end in the post? Were they easy to complete or do you remember them being a problem?

**Table 4 T4:** Interview topic guide for the healthcare professional interviews

The interview will be structured on the following areas of interest	Sample questions
Introduction (Perceived effectiveness)	Overall, could you share your experiences of being involved with our research?
The randomised to either group	How did you feel about 50% of the patients not receiving the JOINT SUPPORT intervention but getting normal care? Did this ‘sit easy’ with you?

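### Dyad interviews run on an end-of-intervention clock, but the topic guide asks about a questionnaire on a randomisation clock, and the visible text gives usual-care dyads no interview time point

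*Protocol article*

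**What the plan says.** **Interview timing.** The Protocol article (Qualitative study, Data collection) says: "Interviews will aim to be conducted up to 6 weeks post-intervention via telephone or video call, at a time convenient to dyads and healthcare professionals". The reason given is that dyads can reflect "once the intervention has ended in a reasonable recall period". No sentence there, or elsewhere in the visible text, places the interview after the 3-month questionnaire.

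**Topic guide.** Table 3 (dyad interviews) has the item "The ease and convenience of the data collection processes (baseline and 3 months) (all participants" and the sample question "How did you manage with the questionnaires we gave you at the start of the study and at the end in the post". The second is in the past tense and assumes that the final questionnaire has already arrived.

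**Questionnaire timing.** The Secondary outcomes section has it posted at 3 months after randomisation, with a telephone reminder if it is not back within 2 weeks. Table 1 gives the follow-up column as "3 months from post-randomisation (±3 weeks".

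**Programme timing.** "The first session will aim to start within 6 weeks from consent" (JOINT SUPPORT training programme). Table 1 places the group sessions in weeks 1 to 5. A therapist then "will telephone each caregiver and patient as a dyad during Week 1, 3 and 6 post-group session discharge" (telephone booster calls).

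**Usual care.** The qualitative Eligibility section plans interviews with about 8 usual-care patients and 8 caregivers. The Usual care section gives that care no end date; its logs run for as long as the patient stays with the service.

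**The concern.** The interview is scheduled from the end of treatment and the outcome questionnaire from randomisation. The gap between those two dates depends on how soon a dyad's first class starts, so the order of interview and questionnaire is left to chance. The topic guide assumes one order only.

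Two things are at stake. First, a dyad interviewed before the questionnaire arrives cannot say how it coped with it. That loses information on follow-up data collection, which bears on the secondary objective of outcome completeness. Second, the interview asks unblinded participants how their allocation felt, what helped, and what was lacking. Held before the only follow-up, it could colour the self-reported outcomes from which the signal of effectiveness is calculated.

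For usual-care dyads the rule does not work as written, because there is no intervention end to count from.

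**Working it through.** There is no figure in the plan to reproduce; this is calendar arithmetic on the stated schedule, followed by a comparison of texts.

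**Inputs**
- *s* = weeks from randomisation to session 1. The protocol counts up to 6 weeks from consent, and the lag from consent to randomisation is not given. Assumption: *s* lies between 0 and 6.
- Group phase: weeks 1 to 5 (Table 1), assumed weekly. The last session is at *s* + 4 (the fifth weekly session) or *s* + 5 (counting to the end of week 5).
- Last booster call: 6 weeks after the last group session.
- Interview window: the 6 weeks after the intervention ends.
- Questionnaire posting: 3 × (365.25/12)/7 = 13.04 weeks. Window: 13.04 ± 3 = weeks 10.04 to 16.04.

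**Formulae**, with the intervention ending at the last booster call
- End of intervention: E = *s* + 4 + 6 = *s* + 10, or *s* + 5 + 6 = *s* + 11.
- Interview window: E to E + 6.
- Interview weeks before posting: max(0, 13.04 − E).

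| *s* | E | Interview window (weeks) | Weeks before posting |
|---|---|---|---|
| 0 | 10 or 11 | 10–16 or 11–17 | 3.0 or 2.0 |
| 1 | 11 or 12 | 11–17 or 12–18 | 2.0 or 1.0 |
| 2 | 12 or 13 | 12–18 or 13–19 | 1.0 or 0.0 |
| 3 | 13 or 14 | 13–19 or 14–20 | 0.0 or 0 |
| 6 | 16 or 17 | 16–22 or 17–23 | 0 or 0 |

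The interview can precede posting only if *s* < 13.04 − 10 = 3.04 weeks, or *s* < 13.04 − 11 = 2.04 weeks. Later starters are interviewed after posting. Some of them may not yet have returned the questionnaire, since its window stays open to week 16.04; this is possible for *s* up to about 6 weeks (16.04 − 10) or 5 weeks (16.04 − 11).

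**Numbers interviewed.** 12 + 8 = 20 dyads, and 20/80 = 25%, if the counts in the qualitative Eligibility section are dyads. The abstract says 24 dyads, which would be 24/80 = 30%. By arm, the 20 dyads are 12/40 = 30% and 8/40 = 20% at 1:1. At 2:1 they are about 12/53 = 23% and 8/27 = 30%, assuming the larger arm is JOINT SUPPORT. These shares count every interviewed dyad, so they are upper limits on the share interviewed early.

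**Can one sequence serve both aims?** For *s* = 0 the planned interview window ends at week 16 or 17, and the questionnaire window closes at 16.04. Even for the earliest starter who never returns the questionnaire, the interview can fall at the very end of the planned 6 weeks (slack 16 − 16.04 ≈ 0, or 17 − 16.04 ≈ 1 week). For *s* = 3 the slack is about 3 or 4 weeks (19 or 20, less 16.04). A questionnaire returned before its window closes leaves more room.

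**The case against.** **The interview is meant to capture recall of the programme.** The protocol chose its timing for that reason, and in a feasibility trial this is a legitimate priority. It stands as a constraint on the fix, not as a reason to leave the order open: the arithmetic shows that the 6-week aim and the ordering can be kept together.

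**The guide is semi-structured.** An item that does not yet apply can be skipped. True, but the 3-month items are addressed to all participants, and a skipped item is lost information.

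**The time point may be given elsewhere.** The cell marks of Table 1 are not visible, including those in the interview rows, and Figure 1 is not shown. A fuller protocol may also define the usual-care time point. This stands, so the claim is only that the visible text gives none. It does not support saying that usual-care dyads may be interviewed at any stage.

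**Classes of three to five dyads take time to fill.** Immediate starts may be uncommon, which makes early interviews less frequent. This stands; their frequency cannot be worked out from the documents.

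**Influence on outcomes is an inference.** The interview is a single optional session of at most 60 minutes, offered in both arms, and Table 3 asks about weaknesses as well as strengths. Clinical outcomes are a secondary signal, reported descriptively without testing, and no progression criterion uses an outcome score. This stands and keeps the second effect modest.

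**Conclusion.** The point holds as a minor scheduling inconsistency. With the last booster call as the end of the programme, the interview window opens up to about 2 to 3 weeks before the questionnaire is posted for dyads starting within about 2 to 3 weeks of randomisation. For later starters it opens after posting. The visible text gives no time point for about 8 usual-care dyads. This rests on weekly sessions and a start 0 to 6 weeks after randomisation.

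A reader might infer more, in four ways that the documents do not support:
- *That interviews fall in weeks 5 to 11, wholly before the questionnaire.* This counts from the last group session. The guide asks about the booster calls, and Table 2 counts them in compliance with the allocated intervention, so the programme is better read as ending with the last call.
- *That about 4 of the 6 interview weeks come first.* This counts from week 11 to the reminder at week 15. Counted to posting, it is 13.04 − 11 ≈ 2 weeks.
- *That a quarter of the trial is exposed.* About 20 of 80 is the number interviewed, not the number interviewed early.
- *That the interviews are an arm-specific co-intervention defeating the protocol's aim to limit expectation bias.* That aim is stated about the wording of the information sheet, and nothing in the documents shows that interviews shift scores. An effect is plausible, but modest.

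**What to change.** In the qualitative Data collection section, replace the single timing rule for dyads with one tied to follow-up:
- **Both arms:** hold the dyad interview after the 3-month questionnaire has been returned or its window has closed.
- **JOINT SUPPORT dyads:** also after the last booster call, still aiming for within 6 weeks of it.
- **Usual-care dyads:** within 6 weeks of questionnaire return or window closure.

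Leave the healthcare professional interviews as planned. If the interview rows of Table 1 mark a time point, bring it into line with the new sentence.

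The cost is one scheduling sentence. For early starters the interview falls later in the planned window, so recall is slightly longer. The slack is almost nil for the earliest starters who do not return the questionnaire, but the 6-week limit is already worded as an aim. The calendar allows it: final follow-up is due by November 2023 and the trial ends in April 2024.

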#### Data analysis

All interviews will be audio-recorded, transcribed and anonymised. After transcription, the audio data will be destroyed. Data will be analysed thematically taking a two-stage approach to understand the important contextual factors that have influenced the implementation of JOINT SUPPORT. We aim to initially analyse all data deductively, guided by the Medical Research Council guidance for complex interventions,^38–40^ to assess the quality of implementation, clarify the hypothesised causal mechanisms identified in our logic model (eg, goal setting in the training and the support provided by the telephone coaching), identify contextual factors associated with variation in outcomes and how the intervention might be optimised for acceptability.^37^ Data will then be analysed more inductively and more broadly. This will include critiquing the conceptual approach of JOINT SUPPORT, understanding any unintended consequences and reflections on the JOINT SUPPORT intervention from the healthcare professional, patient and caregiver perspective.

### Trial status

The trial is funded for 24 months commencing in April 2022. Recruitment is expected to be complete by June 2023 with the final follow-up visit completed by November 2023. The trial will be completed by April 2024.

### Patient and public involvement

Patients have been involved with the study development from inception. Their involvement will continue throughout the trial. A patient-dyad member will attend TOC meetings. They will provide insights into the trial conduct, particularly on data collection processes. They will also help interpret the findings and the dissemination phase.

### Ethics and dissemination

All data will be processed according to the Data Protection Act.^41^ All documents will be stored safely in confidential conditions. Trial-specific documents, except for the signed consent form and follow-up contact details, will refer to the participant with a unique study participant number, not by name. Participant identifiable data will be stored separately from trial data. All trial data will be stored securely in offices or online in secure trial databases, only accessible by the central trial team and authorised personnel. Participant withdrawal is permitted at any point post-enrolment. This will be recorded on a trial CRF, including reasons for withdrawal. Adverse events and serious adverse events will be recorded and reported in-accordance to International Conference on Harmonisation Good Clinical Practice (ICH GCP).^19^

The results of the trial will be reported using the Consolidated Standards of Reporting Trials guidelines^42^ including the relevant extensions for non-pharmacological interventions and for pilot and feasibility studies. The intervention will be reported according to the TIDieR (Template for Intervention Description and Replication) guidelines.^43^ This will be presented to academic, clinical and patient and public audiences. To ensure that outputs are accessible to diverse stakeholder groups, we will develop result materials across our research team including patient representatives.
